## Abstract

**Background:**

Effective and scalable prevention approaches are urgently needed to address the rapidly increasing rates of e-cigarette use among adolescents. School-based eHealth interventions can be an efficient, effective, and economical approach, yet there are none targeting e-cigarettes within Australia. This paper describes the protocol of the OurFutures Vaping Trial which aims to evaluate the efficacy and cost-effectiveness of the first school-based eHealth intervention targeting e-cigarettes in Australia.

**Methods:**

A two-arm cluster randomised controlled trial will be conducted among Year 7 and 8 students (aged 12–14 years) in 42 secondary schools across New South Wales, Western Australia and Queensland, Australia. Using stratified block randomisation, schools will be assigned to either the *OurFutures Vaping Program* intervention group or an active control group (health education as usual). The intervention consists of four web-based cartoon lessons and accompanying activities delivered during health education over a four-week period. Whilst primarily focused on e-cigarette use, the program simultaneously addresses tobacco cigarette use. Students will complete online self-report surveys at baseline, post-intervention, 6-, 12-, 24-, and 36-months after baseline. The primary outcome is the uptake of e-cigarette use at 12-month follow-up. Secondary outcomes include the uptake of tobacco smoking, frequency/quantity of e-cigarettes use and tobacco smoking, intentions to use e-cigarettes/tobacco cigarettes, knowledge about e-cigarettes/tobacco cigarettes, motives and attitudes relating to e-cigarettes, self-efficacy to resist peer pressure and refuse e-cigarettes, mental health, quality of life, and resource utilisation. Generalized mixed effects regression will investigate whether receiving the intervention reduces the likelihood of primary and secondary outcomes. Cost-effectiveness and the effect on primary and secondary outcomes will also be examined over the longer-term.

**Discussion:**

If effective, the intervention will be readily accessible to schools via the *OurFutures* platform and has the potential to make substantial health and economic impact. Without such intervention, young Australians will be the first generation to use nicotine at higher rates than previous generations, thereby undoing decades of effective tobacco control.

**Trial registration:**

The trial has been prospectively registered with the Australian and New Zealand Clinical Trials Registry (ACTRN12623000022662; date registered: 10/01/2023).

**Supplementary Information:**

The online version contains supplementary material available at https://doi.org/10.1186/s12889-023-15609-8.

Despite only emerging in recent years, e-cigarette use, particularly among adolescents who do not smoke, has become a global public health concern [1]. The most recent (2017) representative survey of Australian secondary school students, aged 12–17 years, found 14% had used an e-cigarette, among whom 32% had done so in the past month [2]. Global data suggests these numbers are rapidly climbing, with over 40% of young people in other high-income countries (e.g., the United States [US], France, Italy and Spain) now having used e-cigarettes [3]. This dramatic increase contrasts with the steady declines in youth alcohol and other drug use observed over the past decade [4]. The surge has been fuelled by e-cigarette companies and marketing campaigns targeting youth through the use of bright colours, flavours (e.g., fairy floss), and a strong social media presence. This is problematic as e-cigarettes often contain harmful chemicals and the long-term effects are currently unknown [5]. Although, in Australia, it is illegal to buy or sell e-cigarettes containing nicotine without a prescription [6], they are surprisingly easy to purchase unlawfully from tobacconists, vape stores and online. Further, many e-cigarettes contain high doses of nicotine (up to 50 mg – equivalent to approximately one pack of cigarettes [7]), even when labelled as nicotine free [8]. Nicotine is highly addictive and can impede healthy brain development [9]. Indeed, more than half of adolescent e-cigarette users experience symptoms of nicotine dependence [10].

A major recent review found e-cigarettes can also cause a range of acute health problems, including e-cigarette or vaping use-associated lung injury (EVALI), seizures, poisoning and burns [11]. E-cigarette use has also been associated with mental health problems, such as depression and suicidal ideation in adolescence (although causality has not been established) [12]. Alarmingly, young people who use e-cigarettes are three times more likely to take up tobacco smoking when compared to people who have never used e-cigarettes, putting them at risk of the substantial harm and burden of disease that tobacco smoking can cause [13]. Whilst e-cigarettes may help some individuals to quit smoking, the health risks significantly outweigh any benefits [11]. Despite this knowledge, perceived harm of e-cigarettes by adolescents is low [14], and they are now the most commonly used nicotine product among youth [15]. Effective and scalable interventions are urgently needed to address this critical health issue which has the potential to undo decades of successful tobacco control in Australia.

Drug harm prevention initiatives delivered during adolescence are an efficient and effective way to deliver long-term health and economic benefits [16, 17]. Schools are an ideal setting as they provide an opportunity to reach large numbers of young people and intervene prior to the onset of harmful drug use [2]. In addition, drug education is mandatory within the health curriculum across many countries, including Australia [18]. School-based preventive interventions targeting tobacco, alcohol and other drugs can be effective at preventing, delaying, and reducing substance use and related harms [16, 19]. The strongest evidence exists for interventions that help adolescents overcome social influences to use tobacco or other drugs, and improve social competence, by developing problem solving, decision-making, resistance and assertiveness skills [19, 20]. Such interventions are best implemented alongside policy-level prevention initiatives, such as laws to reduce access, use and supply [21, 22].

Despite the demonstrated potential of school-based substance use prevention, an evidence-practice gap exists, with less than one in four teachers implementing a drug prevention program with evidence of effectiveness [23, 24]. Amongst schools that do deliver evidence-based prevention, many do so ‘off-label’, with teachers making adaptations over 95% of the time, undermining the fidelity and established efficacy of the programs [23, 25]. This is often due to implementation barriers, such as limited time and resources, or a lack of suitability due to end-users not being involved in program design. eHealth interventions can overcome common implementation barriers within the school environment. For example, pre-programmed content reduces reliance on teacher training, and limits the potential for adaptations that could compromise intervention fidelity. Further, online interactive components can increase student engagement, accessibility and scalability [26].

Whilst evidence supports the effectiveness of school-based preventive eHealth interventions in addressing alcohol and other drug use among adolescents [19], there is a dearth of eHealth interventions targeting e-cigarette use. Developed in the US and based on successful tobacco and other substance use prevention techniques, the ‘CATCH My Breath’ intervention is, to our knowledge, currently the only school-based eHealth intervention with demonstrated efficacy at preventing e-cigarette use [27]. However, lessons consist of teacher presentations and peer-led group work which may vary and compromise effectiveness in real-world settings. Moreover, the need for specialised teacher and peer-leader training may limit scalability. An urgent need remains for new scalable approaches to prevent e-cigarette use, specifically within the unique Australian context where it is illegal to buy or sell e-cigarettes containing nicotine [6].

To address these gaps, we developed the first school-based eHealth preventive intervention to target e-cigarette use among young Australians – the *OurFutures Vaping Program*. *OurFutures* is an innovative, universal prevention model that adopts a harm minimisation and comprehensive social influence approach to drug prevention. The model was designed to maximise intervention fidelity and overcome common implementation barriers for school-based interventions. For example, the core intervention component is the cartoon storyboards which cannot be adapted by teachers. The cartoons follow the lives of a group of young people around the same age as the target students who, through their experiences, impart knowledge, skills and values related to alcohol and other drug use. In essence, this provides peer-led education, which is more effective at addressing adolescent substance use compared to adult-led education [28]. Further, online delivery makes the program readily accessible and scalable, regardless of location. To reduce the burden on teachers, the content is aligned with the Health & Physical Education Curriculum and offers a direct replacement for regular health education lessons.

The effectiveness of the *OurFutures* programs has been established through 8 large randomised controlled trials (RCTs) across Australia (240 schools, > 21,000 students). These studies demonstrated that the *OurFutures* programs targeting alcohol, cannabis, psychostimulants and emerging drugs, are more effective than school-based health education as usual in reducing alcohol consumption, binge drinking, cannabis use, ecstasy use, harms from substance use, intentions to use substances, and in increasing knowledge about substance use harms, up to 3 years following intervention delivery [29–31]. Notably, reductions in harmful alcohol use have also been observed up to age 20 (i.e., 7 years following intervention delivery) [16]. Moreover, a recent independent review found *OurFutures* to be one of only two school-based alcohol and other drug education programs in Australia with a strong evidence base [32]. Capitalising on this world-first program of research, we have applied the successful *OurFutures* model to the prevention of e-cigarette use through the *OurFutures Vaping Program*. This study aims to evaluate the efficacy of the program through a multisite cluster RCT. It is hypothesised that compared to an active control group (health education as usual):

students who receive the *OurFutures Vaping Program* will be less likely to commence e-cigarette use at the 12-month follow-up (primary outcome).the *OurFutures Vaping Program* will achieve superior outcomes on secondary outcomes including: uptake of tobacco smoking, frequency/quantity of e-cigarettes use and tobacco smoking, intentions to use e-cigarettes/tobacco cigarettes, knowledge about e-cigarettes/tobacco cigarettes, motives and attitudes relating to e-cigarettes, self-efficacy to resist peer pressure and refuse e-cigarettes, mental health, quality of life, and resource utilisation.benefits of the *OurFutures Vaping Program* on primary and secondary outcomes will be sustained over the long-term (up to 36-months post baseline).the *OurFutures Vaping Program* will demonstrate cost-effectiveness (up to 36 months post baseline).

## Method

### Study design

A two-arm cluster RCT will be conducted among Year 7 and 8 students in 42 secondary schools across New South Wales (NSW), Western Australia (WA) and Queensland (QLD), Australia, from 2023 to 2026. Cluster randomisation at the school level will be used to avoid potential contamination of the control group by the intervention group (e.g., due to student communication). This design allows for optimal and rigorous evaluation of the research questions and hypotheses. Schools will be randomly allocated (1:1) to either the *OurFutures Vaping Program* intervention group or an active control (health education as usual). An economic evaluation will be conducted alongside the cluster RCT to determine the cost-effectiveness of the OurFutures Vaping Program. The study is sponsored by the University of Sydney and has been approved by the Human Research Ethics Committees of the University of Sydney (2022/818), University of Queensland (2023/HE000082) and Curtin University (HRE2023-0059). The trial will follow Consolidated Standards of Reporting Trials (CONSORT) guidelines for cluster RCTs and has been prospectively registered with the Australian and New Zealand Clinical Trials Registry (ACTRN12623000022662), with any modifications logged immediately. This protocol follows Standard Protocol Items: Recommendations for Interventional Trials (SPIRIT) guidelines (see Additional File 1 SPIRIT checklist).

### Sample size calculations

The sample size calculations are based on a method to detect intervention by time interactions in longitudinal cluster RCTs [33]. To detect differences by state, and between groups across the six measurement occasions, six schools and 420 students will be randomly allocated to each of the control and intervention groups in each state (12 schools; 840 students per state). This will achieve 95% power to detect an Odds Ratio (OR) of 0.7 in the primary outcome, which is in line with effect sizes from similar school-based prevention trials targeting tobacco smoking [34, 35]. To account for school dropout (approx. 15%) and student attrition (approx. 25% over 36 months), we aim to recruit a minimum of 14 schools and 1,120 students per state at baseline to test intervention effects (N = 42 schools; 3,360 students). Based on rates in our previous school-based universal substance use prevention trials and successful recruitment strategies [36], we anticipate most, if not all, students will participate.

### Procedure

#### Inclusion and exclusion criteria

Eligible participants will be Year 7 and Year 8 students (aged approximately 12–14 years) attending participating schools in 2023. Students will be required to be fluent in English and provide informed active consent and parental consent to participate. Schools with less than 70 enrolled students per cohort and based outside of NSW, WA or QLD will be excluded.

#### Recruitment

Independent, Government and Catholic secondary schools in NSW, WA and QLD will be invited to participate. Schools that have previously expressed interest in participating in research will be approached and we will simultaneously promote the study through our extensive professional networks via email and social media. Schools will also be approached using publicly available contact details. An invitation will be sent to school principals and health education staff outlining the study aims and seeking permission to implement the study. Research staff will also follow up schools via phone call and email.

#### Randomisation

The *blockrand* package in R [37] will be used to generate an unpredictable, concealed random allocation sequence. After schools’ consent and enrolment in the study, a biostatistician with no role in school recruitment will use the package to block randomise schools to study groups, with stratification by state and school gender mix (coeducational, predominately male [> 60%], or predominately female [> 60%]). Automatic randomisation removes any researcher involvement, and the allocation will be concealed from the investigators and all research personnel (blinded), except those with direct school involvement where blinding is not possible (e.g., Research Assistants who will need to discuss intervention delivery with teachers). Twenty-one schools will be randomly allocated to the *OurFutures Vaping Program* intervention group and 21 schools to an active control group. Figure 1 provides an overview of the anticipated recruitment and randomisation process, and Table 1 presents the SPIRIT flow diagram schedule of enrolment, interventions, and assessments.

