**ASSESSMENT**								
Primary Outcomes			X	X	X	X	X	X
Secondary Outcomes (except RUQ & SDQ)			X	X	X	X	X	X
Secondary Outcomes (RUQ & SDQ)			X	X		X	X	X
Process outcomes				X				

*Note: RUQ = Resource Use Questionnaire; SDQ = Strengths & Difficulties Questionnaire.*

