#### Secondary outcomes

*Tobacco ever use.* Assessed using a single item: “Have you ever tried smoking a cigarette, even one or two puffs?” (Yes/No). This item was based on items used in our previous trials [39] and the Standard High School Youth Risk Behaviour Survey [40].

*Frequency and quantity of e-cigarette and tobacco cigarette use.* Assessed using a series of questions based on those used in previous research [36, 39, 41] and the National Drug Strategy Household Survey [42].

*Knowledge about e-cigarettes and tobacco cigarettes.* Measured using a 15-item scale developed to reflect the content of the *OurFutures Vaping Program* intervention. The scale was derived from a larger pool of items that was piloted among adolescents to reflect items of varying degrees of difficulty. The items assess a range of topics such as the short- and long-term effects/harms of e-cigarettes and tobacco cigarettes, common myths about e-cigarettes and tobacco cigarettes, e-cigarette and tobacco cigarette laws in Australia, and the prevalence of e-cigarette and tobacco cigarette use among young people in Australia. Response options include: True/False/Don’t know.

*Motives to use e-cigarettes.* Assessed using an adapted version of the Tobacco Motives Inventory [43]. The scale comprises 15 potential motives for vaping across four subscales: Social Motives, Self-enhancement Motives, Boredom Relief Motives, and Affect Regulation Motives. Items will be rated on a 5-point Likert scale from 0 (not at all true) to 4 (very true).

*Attitudes towards e-cigarettes.* Assessed using an adapted and validated version [44] of the Smoking Expectancy Scale for Adolescents [45]. The scale includes 43 items relating to the potential consequences of smoking an e-cigarette (e.g., “feel more relaxed”, “get hooked”) across eight subscales: Health Costs, Appearance – Presentation Costs, Social Costs, Addiction, Social Benefits, Affect Control, Boredom Reduction, and Weight Control. Items are rated on a 10-point Likert scale from 0 (completely unlikely) to 9 (completely likely).

*Intentions.* Two single items based on those from our previous school-based trials [36, 39] will be used to assess intentions to use e-cigarettes and tobacco cigarettes in the next year. Responses will be rated on a 5-point scale from 0 (Certain not to try) to 4 (Certain to try).

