#### Additional measures

Additional measures include demographic information comprising age, sex, gender, cultural and linguistic diversity attributes, academic performance, and truancy rates. To measure socioeconomic status, students will complete the Family Affluence Scale III [62] and provide their home postcode, which will be used in addition to each school’s Index of Community Socio-Educational Advantage score. Alcohol use will be assessed using items from our previous trials [39]. Emotional regulation will be measured using the Emotion Regulation Questionnaire for Children and Adolescents [63].

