### Analysis

#### Intervention effects

Data analysis will be conducted on an intention-to-treat basis, whereby all randomised students will be analysed in the groups that they were originally assigned. Generalized mixed effects regression will investigate whether receiving the intervention reduces the likelihood of primary and secondary outcomes (e.g., logistic regression for dichotomous outcomes, poisson regression for count outcomes, linear regression for continuous outcomes). Analyses will be conducted in R, using the *lme4* package [65]. To account for within-person and within-school dependency in the data, models will include participant and school as nested random intercepts; and participant and time as random slopes. We will also test different specifications of time (linear, quadradic & categorical) to determine the best fitting model for the data. Model fit will be compared using likelihood ratio tests, AIC and BIC statistics. The effect of greatest interest will be the time × group interaction for the primary outcome, which reflects the relative average 12-month change in the log odds of the outcome for the intervention group compared to control, adjusting for baseline differences. Due to loss to follow-up, we reasonably expect some outcome data to be missing. Mixed-effects models use maximum likelihood estimation (MLE), producing unbiased estimates when data is assumed to be not missing completely at random. Missing data will be explored by examining baseline differences on the outcome and other potential confounding variables between those retained and those lost to follow-up. Sensitivity analysis will examine the impact of potential covariates related to missingness by including those predictors in the imputation model during multiple imputation.

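### The primary model names no prognostic covariate for the effect estimate, although the school advantage score and baseline vaping intention are collected; pre-specifying both is a cheap and modest gain in precision.

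*Protocol article*

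**What the plan says.** All references are to the protocol article.

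- **Randomisation.** Schools are block randomised "with stratification by state and school gender mix (coeducational, predominately male [> 60%], or predominately female [> 60"%]). "Twenty-one schools will be randomly allocated to the *OurFutures Vaping Program* intervention group and 21 schools to an active control group".
- **Additional measures.** Socioeconomic status is measured partly by each school's "Index of Community Socio-Educational Advantage score" (ICSEA below).
- **Secondary outcomes, Intentions.** Two single items, scored 0 to 4, "will be used to assess intentions to use e-cigarettes and tobacco cigarettes in the next year". Table 1 schedules this group of outcomes from baseline onward. It places student consent and baseline after school allocation, and Table 3 places baseline before the programme.
- **Intervention effects.** For the random part, "models will include participant and school as nested random intercepts; and participant and time as random slopes". The effect of greatest interest is the time × group interaction, "which reflects the relative average 12-month change in the log odds of the outcome for the intervention group compared to control, adjusting for baseline differences". Covariates beyond these terms are mentioned only as possible predictors of missingness, to be put into the imputation model of a sensitivity analysis.

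**The concern.** The primary outcome is uptake, measured by a yes/no item on ever having vaped. A student who can still take up vaping during the trial answered no at baseline. The baseline value is therefore the same for every such student and cannot tell a likely starter from an unlikely one. A time × group contrast removes differences between schools in their stable level of use. It does not remove differences in the rate at which never-users start.

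ICSEA and baseline intention are candidates for explaining that remaining variation, and both are already collected. The section that sets out the primary model gives such variables a role in imputation but none in the estimate. With a few dozen schools, leaving them out may cost some precision and leaves the single realised estimate open to chance imbalance. If the covariates are chosen only after outcomes are seen, the choice is open to the charge of selective adjustment.

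**Working it through.** **1. The plan's own figure.** The only related figure is 95% power for an odds ratio of 0.7. The article gives no alpha, intracluster correlation (ICC), control-arm rate or within-student correlation, so it can be neither confirmed nor refuted. Some inputs do reach it: a change contrast over all states with control rate 14%, within-student correlation 0.8 and ICC 0.01 gives 0.94. Nothing below depends on this figure.

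**2. Chance imbalance in an unstratified school score.** The input is 21 v 21 schools (Randomisation). For a standardised score, ignoring strata:
- SD of the arm difference = √(1/21 + 1/21) = √(2/21) = 0.309
- P(|difference| > 0.5 SD) = P(|Z| > 0.5/0.309 = 1.62) = 0.105
- P(|difference| > 0.25 SD) = 0.42

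**3. Ceiling on the gain, ignoring baseline.** Inputs are 36 schools of 70 students (6 schools and 420 students per arm in each of three states, Sample size calculations). ICC and R², the share of between-school variance explained by the score, are assumed. For a 12-month-only comparison:

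variance ratio = [70·ICC·(1 − R²) + (1 − ICC)] / [1 + 69·ICC]

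| ICC | R² = 0.2 | R² = 0.4 |
|---|---|---|
| 0.01 | 1.55/1.69 = 0.917 | 1.41/1.69 = 0.834 |
| 0.02 | 2.10/2.38 = 0.882 | 1.82/2.38 = 0.765 |
| 0.05 | 3.75/4.45 = 0.843 | 3.05/4.45 = 0.685 |

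The reduction is 8–32%. It overstates the case, because the stated model already uses baseline vaping.

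**4. Gain once baseline use is in the analysis.** These are school-level simulations, and all inputs beyond the design are assumed.
- *36 schools of 60 students, baseline ever-use about 8%, 12-month uptake about 14%, school effects on baseline use and uptake correlated 0.5 or 0.8, score explaining 20–40% of between-school variance in uptake.* Variance of the change contrast falls by 0–9% at ICC 0.02 and 6–18% at ICC 0.05. With baseline as a covariate instead, it falls by 0–9% and 4–16%.
- *A separate run of the change/uptake contrast.* Variance falls by 7–16% if the score explains 40% of between-school variance, and rises by 2–6% if the score is uninformative.
- *A score that predicts only the stable school level.* There is no gain (about −3%). A score explaining 20–40% of the school variance that remains after baseline gives about 10–27%, but that is a stronger assumption.

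The small loss is what theory predicts. One useless school-level covariate with 36 schools inflates the variance by about 1/(36 − 4) = 1/32 = 3.1%.

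**5. Intention.** Explaining 5–10% of within-school variance, it cuts the 12-month variance by about 1–6%. In the change/uptake simulation, intention alone gave about 0–6%.

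**The case against.** **The adjustment set may sit in an analysis plan that is not shown.** This is true, and the article's silence does not prove that the final analysis omits these covariates. What stands is narrower. The article sets out the random effects, the forms of time to be compared, the software and the contrast, and then places extra covariates in the imputation model only. Naming two covariates for the estimate is a concrete change to that text.

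**The model is not unadjusted.** Correct. All randomised students are analysed and no restriction to baseline never-users is stated, so baseline use among ever-users carries school and student information. This is why the gain is small, but it does not help to separate risk among never-users.

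Three stronger readings are tempting, and the document does not support them.

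- *Allocation is at fault.* Intention did not exist when schools were allocated. State and gender mix already give 3 × 3 = 9 strata for 42 schools, under five per stratum, which leaves little room for another factor.
- *The result would be biased.* Chance imbalance under randomisation is already reflected in the standard error, so the test remains valid. The article also gives no figure, and no direction, linking school advantage to vaping.
- *Large gains are at stake.* A 0.5 SD imbalance can be turned into a log odds ratio shift of 0.06–0.13, or 16–37% of |log 0.7| = 0.357. That applies an assumed R² to the whole school SD at ICC 0.02–0.05, not to what is left after baseline. Power gains computed from a single follow-up without baseline do not test the stated model either.

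One caution remains. Baseline intention is measured before the programme but after school allocation, so it is not strictly a pre-randomisation variable.

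**Conclusion.** The point holds as a recommendation on precision. The primary model, as published, names no prognostic covariate for the effect estimate, while two candidates are collected and are given no role in it. The imbalance figure (about a 10% chance of more than 0.5 SD) follows from 21 v 21 schools alone. The benefit depends on assumed inputs: roughly 0–16% lower variance of the arm contrast if ICSEA explains 20–40% of between-school variance in uptake, a few percent lost if it explains none, and about 0–6% from intention alone. Validity is not in question, nothing in the article is contradicted, and no power gain should be claimed.

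**What to change.** Before outcomes are seen, state in the primary analysis that:

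- the fixed part includes school ICSEA (continuous, value held at enrolment) and baseline intention to use e-cigarettes;
- each enters with its interaction with survey wave, in whichever form of time is chosen, because a main effect alone would barely move a time × group contrast;
- the time × group contrast at 12 months stays primary, and a 12-month-only model is not substituted, since that would change the contrast;
- the model without these covariates is reported beside it as a sensitivity analysis;
- missing baseline intention is handled by a simple rule named in advance.

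Allocation is left unchanged. The cost is analysis wording on data already collected, a few extra parameters, a possible loss of a few percent in precision if the covariates prove uninformative, and an odds ratio that is conditional on the covariates. The last is a reason to show the version without them alongside.
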